## Abstract

**Background::**

Halitosis is the term used to define an unpleasant odor emanating from the mouth. However, no studies have evaluated the causes and treatment of halitosis in the population of older adults with denture.

**Methods::**

A randomized, controlled trial is proposed. The patients will be divided into 2 groups: G1: older adults who wear complete dentures and will be treated with tongue scraper (n = 20); G2 older adults who wear complete dentures and will be treated with PDT (n = 20). If the halitosis persists, the participants will be submitted to hygiene procedures for the mucosa and dentures. The evaluation of halitosis will be made before and after treatments, with OralChroma^TM^. If the halitosis is solved, the participants will return after 1 week for an additional evaluation. Oral Health Impact Profile (OHIP-14) will be administered by a calibrated examiner on the day the patient history is taken (baseline) and 1 week after treatment for halitosis.

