### Characterization of the study

2.7

The experimental design will consist of 2 groups: G1-older adults with halitosis (SH2 ≥ 112 ppb) who wear complete dentures and treatment with a tongue scraper (n = 20); G2-older adults with halitosis (SH2 ≥ 112 ppb) who wear complete dentures and treatment with PDT (n = 20). The evaluation of halitosis will be performed at baseline (1st session), after treatment with a tongue scraper or PDT (1st session) and after 1 week (2nd session) (Fig. 3).

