### Assessment of halitosis

2.9

This is the primary outcome of the study. The portable Oral Chroma^TM^ (Abilit, Japan) will be used for the assessment of halitosis, which is a highly sensitive semiconductor gas sensor. The participant was instructed to rinse with cysteine (10 mM) for 1 minute, with the aim of selecting the gases produced by bacteria degradation. A syringe will be placed in the patient's mouth with the plunger completely inserted and the participant will breathe through the nose with the mouth closed for 1 minute, being careful not to touch the tip of the syringe with the tongue. The plunger will then be withdrawn to fill the chamber with air. This procedure will be repeated. The tip of the syringe will be cleaned to remove the saliva. The gas injection needle will be placed on the syringe and the plunger will be adjusted to 0.5 ml. This air will be injected into the input of the device in a single motion. When connected to a computer, the specific software accompanying Oral Chroma^TM^ produces a graph with peaks and values corresponding to the concentrations of VSCs (from 0 to 1000 ppb) with considerable precision after a period of 8 minutes. The results are stored in both the program and the device. As it is a device, Oral Chroma^TM^ is a blind assessor.

To standardize the readings, the exam will be performed in the morning and the participants will be instructed to avoid the ingestion of some strong spices, onion, garlic, and alcohol as well as the use of an antiseptic mouthwash 48 hours prior to the exam. The participants will also be instructed to abstain from coffee, mints, chewing gum, oral hygiene products, and personal hygiene products with perfume (after shave, deodorant, creams, or tonic) and brush only with water on the day of the test as well as not eat anything at least 2 hours prior to the test.^[23–25]^

*Analysis of Oral Health Impact Profile* (OHIP-14 questionnaire): The OHIP-14 is a shortened version of the original OHIP questionnaire used for the evaluation of the impact of oral health on quality of life. The items are distributed among subscales (functional limitation, pain, psychological discomfort, physical disability, psychological disability, social disability, and social handicap). The OHIP-14 will be administered by a calibrated examiner on the day the patient history is taken (baseline) and 1 week after treatment for halitosis.

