### Cleaning of dentures

2.12

The edentulous patients will be instructed to remove their dentures for cleaning. Sterile gauzes soaked in a 2% chlorhexidine solution will be applied over the entire inner and outer surfaces of the dentures. The mucosa of the edentulous patients will be cleaned with 0.12% chlorhexidine. After cleaning of the mucosa and dentures, patients will rinse with water for 1 minute.

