### Statistical analysis

2.13

The Lilliefors test will be used to determine the normality of the data. If normality is demonstrated, analysis of variance (*t* test student, Bioestat 5.3, Pará, Brazil) will be used to compare continuous and dependent variables among G1 and G.2. If non-normal distribution is demonstrated, Mann Whitney test will be used. The baseline data will be compared to the data collected at 1 week follow-up evaluation. A *P*-value < .05 will be considered indicative of statistical significance. The *χ*^2^ test will be used to compare categorical variables among G1 and G2, at baseline and the 1 week evaluation. These data will be expressed as mean ± standard deviation.

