### Strategies for obtaining the adequate recruitment of the participants

2.14

The participants will be recruited from the clinics of *Universidade Nove de Julho*. A researcher ([name]) will perform the exam to detect halitosis in a reserved room at the university. Treatment will be performed immediately after the diagnosis. The participants will be counseled with regard to oral health and will receive a set of instructions for performing daily oral hygiene. If they wish to withdraw their consent, there will be no loss for them. It is expected that patients will complete their participants, due to the benefit of halitosis reduction. Data from those who discontinue will not be used for analysis. After 1 week, all patients will be asked to return to *Universidade Nove de Julho* for the reevaluation of halitosis.

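### As the abstract reads, the 1-week comparison includes outcome-dependent rescue cleaning and is not PDT versus scraper alone; the text conflicts on who is cleaned and who returns, and any bias is of unknown size and may be nil

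*Protocol article*

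**What the plan says.** The methods paragraph of the abstract sets a rule that depends on the outcome of the allocated treatment: "If the halitosis persists, the participants will be submitted to hygiene procedures for the mucosa and dentures". It continues: "If the halitosis is solved, the participants will return after 1 week for an additional evaluation".

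Section 2.12 describes the procedure. "The edentulous patients will be instructed to remove their dentures for cleaning", the dentures are wiped with 2% chlorhexidine, and "The mucosa of the edentulous patients will be cleaned with 0.12% chlorhexidine". The section does not mention persistence and gives no time.

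On timing, section 2.14 says "Treatment will be performed immediately after the diagnosis". Section 2.7 lists halitosis readings at baseline, "after treatment with a tongue scraper or PDT (1st session) and after 1 week (2nd session"). It has two sessions and no separate reading after cleaning. Section 2.14 asks all patients back at 1 week.

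On analysis, section 2.13 says "The baseline data will be compared to the data collected at 1 week follow-up evaluation". Its sentence on the t test between G1 and G2 names no time point. Section 2.9 has OHIP-14 given "on the day the patient history is taken (baseline) and 1 week after treatment for halitosis".

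**The concern.** The stated aim is to compare PDT with a tongue scraper. Under the abstract's rule, a participant for whom the allocated treatment fails receives a second, antiseptic treatment directed at another possible source of odour. If that happens in session 1, the 1-week reading reflects the allocated treatment plus a rescue, and the share rescued can differ between arms.

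Two things are at stake. The first is what the 1-week result means: it would compare PDT followed by cleaning where needed with scraping followed by cleaning where needed. A null result could then reflect equal efficacy or rescue in the weaker arm. The second is consistency: the visible text disagrees on who is cleaned (abstract versus 2.12) and on who is measured at 1 week (abstract versus 2.14).

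H2S has a reading after treatment in session 1 that could separate these explanations, but 2.13 does not name it. OHIP-14 has no reading between treatment and the possible cleaning.

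**Working it through.** **1. When does cleaning happen?** Diagnosis and treatment take place together (2.14), and a reading follows treatment in session 1 (2.7). The abstract then splits participants into persisting and solved, and sends the solved group to a visit one week later. The split is therefore made before that visit, most naturally on the session 1 post-treatment reading. This is an inference; no visible sentence states it.

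**2. Who is cleaned and who returns?**

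| Reading | Cleaned | Read at 1 week | Consequence |
|---|---|---|---|
| Abstract alone | persisters | solved (persisters not mentioned) | selection on outcome, if persisters have no reading |
| Body alone (2.12, 2.14) | everyone, as worded | everyone | no difference in cleaning between arms |
| Abstract's cleaning rule with 2.14's return rule | persisters | everyone | outcome-dependent rescue inside the 1-week contrast |

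The rest of this check takes the third row.

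**3. Direction.** Let d be the true scraper-minus-PDT difference at 1 week in SD units, q_S and q_P the shares persisting after scraper and PDT, and R the cleaning benefit still present at 1 week. Then

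observed difference = d − (q_S − q_P) × R.

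The bias is zero if R = 0 or q_S = q_P. With d > 0 (PDT better at 1 week), the difference shrinks if q_S > q_P and grows if q_S < q_P.

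**4. Inputs.** The plan gives 18 per group by calculation and 20 per group enrolled. The 18 cannot be reproduced, because the means, variances and power are not in the text. Solving backwards at an assumed 80% power and two-sided 5%, a t test with 18 per group detects d = 0.961; with 20 per group that d has 84% power. The values of q, R and the correlation below are assumptions.

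**5. Illustration in SD units.** The true difference is 0.961 at both readings. A persistence cut-off that leaves 60% above it after scraper leaves 24% above it after PDT: 20 × 0.60 = 12 versus 20 × 0.24 = 4.8, about 5 participants cleaned. Cleaning also changes the spread within arms, so power was simulated (40,000 trials per cell) at several correlations between the immediate and 1-week readings.

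| R (SD) | 0.961 − 0.36 × R | Power, corr. 1.0 | corr. 0.7 | corr. 0.5 |
|---|---|---|---|---|
| 0 | 0.96 | 84% | 84% | 84% |
| 0.5 | 0.78 | 83% | 77% | 73% |
| 1.0 | 0.60 | 75% | 59% | 51% |
| 1.5 | 0.42 | 50% | 32% | 27% |

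With 40% versus 11% persisting, the difference is 0.82, 0.67 or 0.53 SD for R = 0.5, 1 or 1.5, and power at correlation 0.7 is 79%, 66% or 45%. If everyone is cleaned, 0.96 SD and 84% remain.

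**6. Check on the ppb scale.** A separate simulation used log H2S, the 112 ppb threshold as trigger, and assumed effects that leave about 70% (scraper) and 38% (PDT) persisting. Without a cleaning effect, the scraper/PDT geometric mean ratio at 1 week is 1.82 (power 75%). If cleaning lowers H2S in persisters by a factor of 1.5, 2 or 3 at 1 week, the ratio is 1.60, 1.46 or 1.28 and power 65%, 50% or 24%.

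**7. The opposite sign.** Exchange the shares in step 5, so that PDT has more immediate persisters (60% versus 24%) but is still better at 1 week. R = 0.5 then gives 0.961 + 0.36 × 0.5 = 1.14 SD: the difference is exaggerated.

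**The case against.** The strongest reply is that no bias has been shown. Cleaning before the 1-week reading is inferred, and the activity flowchart (Figure 2) and SPIRIT figure (Figure 3), where such a step would normally be placed, were not available. The mechanism also needs the abstract's cleaning rule joined to the body's return rule. Carryover has little support: the introduction says H2S comes mainly from the dorsum of the tongue, whereas cleaning is applied to dentures and mucosa, and the protocol's own restriction on antiseptic mouthwash before a reading is 48 hours, far shorter than a week. Two of the three cleaning effects modelled are larger than the whole assumed treatment difference. Finally, comparing strategies that include rescue is a legitimate design, and an uncontaminated H2S reading is already scheduled.

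Most of this stands. A reader might infer that the 1-week difference will be pulled toward zero and power lost. The documents do not support that: they give no persistence rates and no duration of effect, and step 7 of the working shows that the sign can reverse.

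Some of the concern remains. The introduction also says that complete dentures may favour halitosis, and a mouthwash restriction does not settle how long a disinfected denture stays clean. A strategy comparison is legitimate when it is labelled as one, but the stated aim is PDT versus scraper. The scheduled session 1 reading is not excluded by 2.13, but it is not named there either. The conflicts on who is cleaned and who returns lie in the visible text and are more than the condensation of an article.

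**Conclusion.** The point holds in a limited form. Followed as the abstract is written, with everyone recalled as in 2.14, the 1-week H2S and OHIP-14 contrasts compare strategies that include outcome-dependent chlorhexidine cleaning and do not isolate PDT versus scraper. This rests on cleaning taking place in session 1, which the text suggests but does not state. If Figures 2 and 3 place it after the 1-week reading, only a correction of the wording is left; if 2.12 means that everyone is cleaned, the arms do not differ in cleaning and the abstract is wrong.

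The effect on the estimate is conditional. It needs a cleaning effect that lasts a week and unequal persistence, and it runs toward zero only if the arm with more persisters is also the worse arm at 1 week. Under the assumed values it ranges from nothing to a fall from 0.96 to 0.42 SD, the lower end requiring a carryover of 1.5 SD that nothing in the documents supports. These figures show how the mechanism works and do not estimate what this trial will lose. The change is worth making because the ambiguity concerns who receives an active treatment and the remedy is nearly free.

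**What to change.** Make the abstract, 2.12 and 2.14 agree on who is cleaned and when, and state that all participants return at 1 week, which removes the abstract's condition on return. If Figure 2 already fixes the timing, bring the text into line with it. Then choose one of two options.

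(a) Keep cleaning in session 1, but only after the post-treatment reading. In 2.13, name the between-arm H2S comparison at that reading as the PDT-versus-scraper analysis, and label the 1-week H2S and OHIP-14 results as comparisons of strategies that include rescue cleaning. This costs one more analysis of data already collected. OHIP-14 would still have no reading that isolates the allocated treatment.

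(b) Give cleaning only after the 1-week reading and OHIP-14, to participants whose H2S is still 112 ppb or more. Both 1-week outcomes then reflect the allocated treatment. Participants with persisting halitosis wait one week, with the daily oral hygiene instructions of 2.14 in the meantime, and no scheduled reading follows cleaning, so its success goes unmeasured unless a reading is added.

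Neither option needs more patients or an extra visit.

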**Discussion::**

This protocol will determine the effectiveness of photodynamic therapy regarding the reduction of halitosis in older adults with complete denture.

**Trial registration::**

This protocol was registered in ClinicalTrial.gov, under number NCT03960983. It was first posted and last updated in May 23, 2019. https://clinicaltrials.gov/ct2/show/NCT03960983.

## Introduction

1

Halitosis is a term used to define a transitory or prolonged unpleasant odor emanating from the mouth or breath.^[1,2]^ The prevalence of this condition is not well established, but there are reports of 15% to more than 50% of the population worldwide,^[3–5]^ with a nearly threefold higher incidence among men compared to women, independently of age.^[6,7]^ There is a correlation between older age and bad odor with aging, resulting in increased odor intensity.^[8]^

Few studies have analyzed the prevalence of halitosis in the population of older adults, which is defined by the World Health Organization as individuals aged 60 years or older.^[9]^ The increase in older adults at medical and dental offices underscores the need for greater attention to the adverse health conditions that affect this age group, considering the relationship between halitosis and both oral health and systemic conditions.^[10]^ In Thailand, researchers report a high incidence of halitosis in older adults.^[11]^ In Turkey, this condition was identified mainly in older females who wear complete dentures.^[12]^

Halitosis can exert a negative impact on social aspects, thereby affecting one's quality of life.^[13]^ This condition has a multifactor etiology. It is estimated that the source is intraoral in 90% of cases, resulting from bacterial degradation, especially anaerobic Gram-negative bacteria (*Treponema denticula, Porphyromonas gingivalis, Tannerella forsythia*), which produce volatile sulfur compounds (VSCs) on different surfaces of the oral cavity, such as biofilm on the dorsum of the tongue and in periodontal pockets.^[6,14]^ The VSCs produced through the metabolism of Gram-negative bacteria are hydrogen sulfide (SH_2_), emanated mainly from the dorsum of the tongue, with values higher than 112 ppb indicative of halitosis, methanethiole (CH_3_SH), which is predominantly higher in periodontal pockets, with values up to 26 ppb considered normal, and dimethyl sulfide (CH_3_SCH_3_), which can be of either a periodontal origin or systemic origin (intestinal, hepatic or pulmonary) and has a very low perception threshold (8 ppb). VSCs not only contribute to halitosis, but also result from the formation of volatile aromatic compounds, such as organic acids, acetic acid, propionic acid and the amines cadaverine, and putrescine. The production of VSCs in the oral cavity also depends on local factors, such as saliva, a reduction in the concentration of oxygen in the oral cavity as well as bacterial proliferation and metabolism.^[5,13,15–17]^ Therefore, the conditions that favor the retention of bacterial biofilm (dentures) and poor hygiene constitute predisposing factors for halitosis.^[5]^ Total dentures may favor the appearance of halitosis.^[8]^ Total denture hygiene is related to age, sex, and nocturnal use.^[9]^ The number of denture wearers and individuals with poor oral hygiene is high in the population of older adults, which favors the occurrence of halitosis.^[18]^

Only 8% of cases of halitosis are caused by extra-oral factors. Respiratory, gastrointestinal, hepatic, endocrine, and metabolic disorders have been associated with this condition.^[5,6,13]^

Halitosis can be diagnosed with 3 methods: the organoleptic test, gas chromatography, and a portable gas analyzer.^[13,14,19]^ The gold standard for this diagnosis is gas chromatography.^[17]^ The Halimeter and Oral Chroma are electronic equipment capable of detecting some exhaled VSCs.^[17,19]^ Oral Chroma is a device that specifically identifies VSCs (hydrogen sulfide, methanethiol, and dimethyl sulfide) through a sulfur detector, analyzes breath, and volatile compounds produced by detritus (decomposing food scraps) on the tongue and in saliva, but does not detect other possible causes of halitosis.^[17]^

Treatment for halitosis is related to its etiology. When intraoral, conventional therapy involves a reduction in microorganisms with the use of mouthwashes with antiseptic characteristics combined with mechanical removal using tongue scrapers or brushes, as the dorsum of the tongue is one of the main sources of bacterial colonization.^[13,19–21]^

Antimicrobial photodynamic therapy (PDT) is a treatment option for reducing the amount of intraoral microorganisms in localized infections.^[22–26]^ With this method, there are no reports of bacterial resistance, there are no side effects, the oral microbiota is preserved and toxicity to humans is minimal.^[22]^ PDT consists of the combination of a photosensitizing agent and light at a wavelength of 630 to 830 nm in the presence of oxygen.^[27]^ Despite the advantages of this method, there are no well-designed studies on PDT for the treatment of halitosis in older patients.^[28]^ Only 2 studies have addressed the treatment of halitosis with PDT in healthy adolescents and patients with multiple sclerosis,^[25]^ achieving favorable results. No studies have investigated the effects of PDT for the treatment of halitosis in older adults with denture.

The aim of the proposed study is to evaluate the treatment of halitosis using PDT or a tongue scraper in older adults with complete denture, as this population has not previously been studied.

## Methods/design

2

A single-center, randomized, controlled, single-blind clinical trial was designed in accordance with the criteria recommended for interventional trials in the SPIRIT Statement. The project for the proposed study received approval from the Human Research Ethics Committee of *Universidade Nove de Julho* (certificate number: 12416619.1.0000.5511). This protocol was registered in ClinicalTrial.gov, under number NCT03960983. It was first posted and last updated in May 23, 2019.

### Selection of individuals – characterization of sample

2.1

Two groups will be composed of older adults (60 years or older) in treatment at the dental clinic of *Universidade Nove de Julho.* Since they are already in treatment in the clinic, this will make recruitment simpler. After verbal and written explanations of the study, those who agree to participate will sign a statement of informed consent approved by the Human Research Ethics Committee of *Universidade Nove de Julho*. The study will be conducted in compliance with the precepts stipulated in the Declaration of Helsinki (revised in Fortaleza, Brazil, 2013).

### Calculation of sample size

2.2

To calculate the sample size we established an error *err* = *x*_1_−*x*_2_ where *x*_1_ and *x*_2_ are the mean values of groups G1 and G2, whose variances are 

, respectively. The effect size was calculated by: 
[figure not shown]

If the normal distribution hypothesis is rejected, the sample size should be corrected by approximately 5%.

Observing statistical samples from the reference Mota et al^[14]^; to estimate the mean values and sample variance we obtain the following sample sizes for each group. G1: 18; G2: 18 (Fig. 1).

**Figure 1 F1:**
[figure not shown]
Sample size graph.

### Inclusion criteria

2.3

Men and women aged 60 years or older using complete dentures.

### Exclusion criteria

2.4

Dentate patients and edentulous with no complete denture hypersensitivity to the photosensitizing agent used in PDT, H_2_S < 112 ppb.

### Training and calibration of examiner

2.5

An examiner (gold standard) will perform training and calibration exercises to maximize the reproducibility of the measurements. For such, 10 individuals with halitosis will be evaluated using the Oral Chroma device. These individuals will not participate in the main study. The intraclass correlation coefficient (ICC) will be calculated for the determination of intra-examiner agreement (≥0.90) with regard to the halitosis readings.

### Randomization

2.6

The 40 individuals with complete denture will be randomized in 2 groups: Group A (20 individuals submitted to treatment with a tongue scraper) and Group B (20 individuals submitted to treatment with PDT) (Fig. 2). Opaque envelopes will be identified with sequential numbers (1–40) and will contain pieces of paper with the information of the corresponding experimental group (A or B). Blocked randomization will be performed in blocks of 5 patients (8 blocks for both treatments; example of a block: AABAB). The envelopes will be sealed and kept in numerical order in a safe place until the time of the treatments. The randomization and preparation of the envelopes will be performed by a researcher who will not otherwise participate in the study. Randomization will be performed using Microsoft Excel, version 2013.

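### A single fixed block size of 5, with an operator who sees each treatment, makes some late-in-block allocations predictable: about 4 to 6 of 40 under a 20:20 scheme, 12 if every block is 3:2

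*Protocol article*

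**What the plan says.** Section 2.6 (Randomization) sets the arm sizes: "The 40 individuals with complete denture will be randomized in 2 groups: Group A (20 individuals submitted to treatment with a tongue scraper", with the other 20 receiving photodynamic therapy (PDT). It then fixes the block scheme: "Blocked randomization will be performed in blocks of 5 patients (8 blocks for both treatments; example of a block: AABAB". The composition of the other blocks is not stated.

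The same section describes the safeguards. The assignments are held in numbered, opaque containers, and storage is specified as follows: "The envelopes will be sealed and kept in numerical order in a safe place until the time of the treatments". The list and the envelopes are the work of someone with no further role in the trial.

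Other sections give the setting. Section 2 calls the trial single-centre and single-blind, and section 2.9 names only the measuring device as a blind assessor. Sections 2.10 and 2.11 describe a tongue scraper against methylene blue plus laser. Participants come from the university's own dental clinic: "Since they are already in treatment in the clinic, this will make recruitment simpler" (section 2.1). Section 2.14 adds: "Treatment will be performed immediately after the diagnosis".

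**The concern.** A sealed envelope hides the paper inside it. It does not hide what follows from counting. With a constant block size and one running sequence, a person who has seen the earlier treatments in a block knows the rest of the block once one arm's places are used up. Here the two treatments cannot be mistaken for each other by whoever gives them, and the pool of candidates is already attending the clinic, so there is some freedom over who is invited next and when.

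Foreknowledge of the next assignment allows selection: a patient with a heavier tongue coating, dirtier dentures or a lower chance of returning could be placed in a chosen slot. With 20 per arm, a few such patients could shift the comparison. The comparison described in section 2.13 is a t test or Mann-Whitney test between groups, which gives no protection against this.

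The problem is separate from the imbalance that an odd block size causes. A repair aimed only at the imbalance, such as fixed blocks of 4, would leave predictability in place.

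**Working it through.** **Inputs (section 2.6).** 40 patients; target 20 A (scraper) and 20 B (PDT); 8 blocks of 5; example block AABAB, which is 3 A and 2 B. The composition of the other blocks is an assumption, so the range is shown.

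**The plan's own figures.** 8 × 5 = 40, which agrees. Arm sizes if every block is like the example: 8 × 3 = 24 and 8 × 2 = 16, not 20 and 20. The 20:20 target needs four 3:2 and four 2:3 blocks: 4 × 3 + 4 × 2 = 20 per arm.

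**Certain allocations, composition known.** In a random order of a A's and b B's, every allocation after one arm is exhausted is certain. The expected number is a/(b+1) + b/(a+1).

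- All blocks 3:2: 3/3 + 2/4 = 1.5 per block; 8 × 1.5 = 12.0 of 40. This is a mean. The range is 8 to 24, and the probability of more than 12 is 0.376.
- Fixed blocks of 4 (2:2): 2/3 + 2/3 = 1.33 per block; 10 × 1.33 = 13.3 of 40.
- One list of 20 A and 20 B: 20/21 + 20/21 = 1.9 of 40.

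**Certain allocations, mixed 3:2 and 2:3 blocks.** If the observer does not know which type a block is, the rest is certain only once three of the same arm have been seen. What remains then is the minority arm: 2/4 = 0.5 per block, so 8 × 0.5 = 4.0 of 40 (range 0 to 16).

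If the observer also knows that there are exactly four blocks of each type, the final blocks have known composition once one type is used up. The expected number of such blocks is 4/5 + 4/5 = 1.6, and each gains 1.5 − 0.5 = 1.0 certain allocation: 4.0 + 1.6 = 5.6 of 40.

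**Best guess at every allocation.** Enumerating all orders, and always guessing the likelier arm given what has been seen:

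| Scheme | Certain of 40 | Correct guesses of 40 |
|---|---|---|
| All blocks 3:2 (arms 24:16) | 12.0 | 28.8 (72%) |
| Mix of 3:2 and 2:3, type unknown | 4.0 | 24.8 (62%) |
| Four of each type, known | 5.6 | 26.1 (65%) |
| Fixed blocks of 4 | 13.3 | 28.3 (71%) |
| One list, 20 A and 20 B | 1.9 | 23.5 (59%) |

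Pure chance is 20 of 40.

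**Gain from the single list.** Against mixed blocks: 4.0 − 1.9 = 2.1 to 5.6 − 1.9 = 3.7 fewer certain allocations, and 24.8 − 23.5 = 1.3 to 26.1 − 23.5 = 2.6 fewer correct guesses. Against all-3:2 blocks: 12.0 − 1.9 = 10.1 fewer certain and 28.8 − 23.5 = 5.3 fewer correct guesses.

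**The case against.** The strongest reply is that fixed blocks with sealed envelopes are common in small trials, and that the concealment procedure here is properly described: numbered, opaque, sealed, stored until treatment, and prepared by someone with no other role. Entry also depends on a device reading (H2S of at least 112 ppb), which narrows the room for choosing patients, and baseline readings are taken, so measured imbalance could be adjusted for in part.

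Much of this stands. A reader might go further than the text allows in four ways.

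- That all staff can work out the next assignment. Prediction needs someone who knows the block size, follows the past treatments and can influence the order of enrolment. The protocol does not say who was told the scheme, and section 2.14 does not say who recruits or who treats.
- That allocation concealment fails. What the text supports is partial predictability.
- That the trial is open-label. The protocol says single-blind; what follows from the treatments is only that the operator is not blind.
- That 12 of 40 is a ceiling or the natural estimate. It is a mean, and it needs every block to be 3:2, which conflicts with the stated 20:20.

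What does not stand is that the safeguards remove the problem. The envelopes do not prevent counting, and the H2S threshold does not control which eligible patient is invited next. Adjustment cannot reach characteristics that were not measured.

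**Conclusion.** The point holds as one of partial, avoidable predictability. To a person who knows the scheme and sees past treatments, about 4 to 6 of 40 allocations are expected to be certain if the blocks mix 3:2 and 2:3 to reach 20:20. The figure is 12 of 40 only if all blocks follow the example, in which case the arms are 24:16. The figures assume that every order within a block is equally likely, and they depend on what the observer knows of block composition, which the protocol leaves open. They count opportunities for selection; they do not show that any would be used. The issue is worth correcting because the remedy is almost free and also settles the arm sizes, but under the 20:20 reading the improvement is modest.

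**What to change.** Before enrolment, have the independent researcher replace the blocks of 5 with one random permutation of 20 A and 20 B. Do not disclose the scheme to those who recruit, examine or treat. Section 2.6 should then describe the single list and drop the block size and the example block.

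This lowers predictability under every reading of the present text and guarantees 20:20 if all 40 are enrolled. Fixed blocks of 4 are not an adequate substitute (13.3 of 40 certain). Randomly varied even blocks, for example 4 and 6, would cut certain allocations to about 2 but leave about 27.5 of 40 guessable to someone who knows the sizes, which is more than under the mixed blocks of 5.

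The cost is regenerating one list and its envelopes. The one drawback is slightly looser balance between the arms over calendar time, which matters little in a single-centre trial of this size with 1 week of follow-up.

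### Eight blocks of 5 cannot be balanced between two arms, and nothing in the Randomization section secures the stated 20 versus 20

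*Protocol article*

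**What the plan says.** Section 2.6 (Randomization) of the protocol article fixes the total and the arm sizes: "The 40 individuals with complete denture will be randomized in 2 groups", with "Group A (20 individuals submitted to treatment with a tongue scraper") and "Group B (20 individuals submitted to treatment with PDT"). The Abstract and section 2.7 repeat 20 per group.

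The same paragraph of section 2.6 fixes the method: "Blocked randomization will be performed in blocks of 5 patients (8 blocks for both treatments; example of a block: AABAB"). There is one numbered envelope list for both arms: "Opaque envelopes will be identified with sequential numbers (1–40"). A researcher with no other part in the study prepares the envelopes, and they are sealed ahead of treatment.

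Section 2.2 (Calculation of sample size) gives the number needed: "we obtain the following sample sizes for each group. G1: 18; G2: 18". It adds a correction of about 5% if normality is rejected. Section 2.14 says that data from participants who discontinue are left out of the analysis.

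**The concern.** Blocking in a 1:1 trial is meant to bring the two arms level at the end of every block, and so at the end of the list. A block of 5 cannot do this with two arms. The one example has three A and two B. A person who builds the list from section 2.6 has no instruction that leads to 20 and 20, and permuting the example in every block would lead elsewhere.

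What is at stake is whether the written procedure produces the allocation that the article reports in three places. Because the envelopes are prepared and sealed in advance, an uneven list would be fixed from the first participant on.

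**Working it through.** **Inputs.** Section 2.6: 40 participants, 20 per arm, 8 blocks, 5 per block, example AABAB. Section 2.2: 18 per group, with a 5% correction for non-normality. Section 2.13: significance level 0.05, taken here as two-sided because the sidedness is not stated.

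**Step 1: the total.** 8 × 5 = 40. This reproduces the stated total.

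**Step 2: the split.** AABAB holds 3 A and 2 B. Take each block as 3A:2B or 2A:3B, the closest to balance that 5 allows. Let k be the number of 2A:3B blocks among the eight. Then

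- A = 3(8 − k) + 2k = 24 − k
- B = 2(8 − k) + 3k = 16 + k

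| k | A (scraper) | B (PDT) |
|---|---|---|
| 0 | 24 | 16 |
| 2 | 22 | 18 |
| 4 | 20 | 20 |
| 6 | 18 | 22 |
| 8 | 16 | 24 |

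The stated 20:20 needs k = 4 exactly. The section does not state k, so its figures neither produce 20:20 nor rule it out.

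**Step 3: how often 20:20 would occur by chance.** This needs an assumption that the article does not make: the majority arm is drawn independently for each block with probability 1/2, so k ~ Binomial(8, 1/2).

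- P(20:20) = C(8,4)/2⁸ = 70/256 = 27.3%
- P(PDT below 18), k = 0 or 1: (1 + 8)/256 = 3.5%
- P(either arm below 18): 2 × 9/256 = 7.0%

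**Step 4: what the extreme split does to power.** With equal variances, the equivalent equal-arm size of 24:16 is

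2 / (1/24 + 1/16) = 19.2 per arm.

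This is above 18 and above 18 × 1.05 = 18.9. The effect size and power behind the 18 are not in the visible text, so I solved for the standardised effect that 18 per arm detects at an assumed power, using d = (z₀.₉₇₅ + z_power) × √(2/18), and then computed power at other splits.

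| Assumed power at 18:18 | d | Power at 20:20 | Power at 24:16 |
|---|---|---|---|
| 80% | 0.934 | 84.0% | 82.5% |
| 90% | 1.081 | 92.7% | 91.7% |

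Even the extreme split costs 1.0 to 1.5 percentage points against 20:20 and stays above the power at 18:18, before dropout.

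**The case against.** The strongest reply is that AABAB is labelled an example, and that 20 per arm is stated in the same paragraph. Four 3A:2B blocks and four 2A:3B blocks satisfy every number given: eight blocks, five per block, 40 in total, 20 per arm. On this reading the figures do not contradict each other, and a condensed article has merely left out the mixing rule. A 3:2 block is also within one participant of balance, so blocks of 5 still spread the arms over time.

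Much of this stands. A reader might infer from the example that the trial will end at 24 versus 16, with PDT short of the 18 required. The article does not support that: it never says that all blocks have the example's composition. Nor would 24:16 leave the trial underpowered, because the larger scraper arm more than makes up for the smaller PDT arm (19.2 per arm in equivalent size). The 27% and 7% rest on an assumed coin toss per block and describe that assumption, not the article's method.

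What does not stand is the claim that this is only an omitted detail. The article itself chooses the block size, the number of blocks and the example. Those choices rule out exact balance at the end of any block, and they reach 20:20 only under a condition that is not written down.

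**Conclusion.** The point holds as a badly fixed design parameter. With two arms and blocks of 5, no block can be 1:1. The written procedure allows splits from 20:20 out to 24:16 in either direction, and nothing in section 2.6 selects 20:20. Under the coin-toss assumption, 20:20 would arise about one time in four (27%).

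The consequence is limited. Power is not materially harmed, given equal variances and before any dropout, and nothing here shows bias. The defect is that the stated procedure does not guarantee the stated group sizes or balance at the end of each block. It is worth correcting because the remedy is simple and the envelopes are sealed in advance.

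**What to change.** Before the envelopes are used, replace the blocks of 5 with randomly mixed even block sizes, half A and half B in each, summing to 40. For example, four blocks of 2, five of 4 and two of 6 give 8 + 20 + 12 = 40 and exactly 20:20. Withhold the block sizes from recruiting and treating staff: the operator sees whether a scraper or a laser is used, and a known fixed size of 4 would reveal the last assignment in every block. Correct the example, for instance to ABBA.

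If blocks of 5 are kept, the least that section 2.6 should say is that four blocks are 3A:2B and four are 2A:3B, in random order. That secures 20:20 at the end of the list but not level arms along the way: if the four A-heavy blocks came first, the count after 20 participants would be 12:8.

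The cost is one regenerated list and 40 refilled envelopes, provided that enrolment has not started. The article does not say whether it has.
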